## Abstract

**Abstract:**

**Introduction:**

Serous endometrial intraepithelial carcinoma (SEIC) is a rare, non-invasive lesion of the endometrial epithelium, typically characterised by p53 abnormalities. Although regarded as a precursor lesion, recent classification systems increasingly position SEIC within the broader spectrum of serous carcinomas and current guidelines place non-invasive p53-abnormal serous lesions in an uncertain risk category due to limited outcome data. As a result, SEIC is not consistently addressed as a distinct diagnosis, contributing to variation in clinical management. Complete surgical staging, including pelvic and para-aortic lymph node assessment, is frequently performed, yet supporting evidence remains scarce. This study aims to collect longitudinal data to evaluate surgical management strategies in relation to clinical outcomes, survival and quality of life.

**Methods and analysis:**

This multicentre prospective observational cohort will enrol patients diagnosed with SEIC or equivalent non-invasive serous lesions who provide informed consent. Data will be collected using electronic case report forms (Castor Electronic Data Capture). Baseline clinical, pathological, molecular and treatment data will be collected, including imaging, histopathology, immunohistochemistry and molecular classification when available. Patient-reported outcomes will be assessed using the European Organisation for Research and Treatment of Cancer Quality of Life Questionnaire Core 30 (EORTC QLQ-C30), European Organisation for Research and Treatment of Cancer Quality of Life Questionnaire Endometrial Cancer Module (EORTC QLQ-EN24) and EuroQol 5-Dimension 5-Level questionnaire (EQ-5D-5L) questionnaires at baseline, 6 months, 2 years and 5 years after diagnosis. The primary outcome is progression-free survival, secondary outcomes include overall survival, health-related quality of life and adverse events. Analyses will be primarily descriptive. Survival outcomes will be estimated using Kaplan-Meier methods, with Cox proportional hazards modelling used to explore predictors of outcome where feasible.

**Ethics and dissemination:**

The study will be conducted in accordance with the Declaration of Helsinki and applicable regulations. Ethical approval was obtained at the Erasmus MC (MEC-2025-0368). Results will be disseminated through peer-reviewed publications and scientific meetings.

**Trial registration number:**

NCT06677242.

STRENGTHS AND LIMITATIONS OF THIS STUDYThis prospective multicentre registry is specifically designed for patients with serous endometrial intraepithelial carcinoma (SEIC) and equivalent non-invasive serous endometrial lesions.Standardised collection of clinical, pathological, molecular and patient-reported outcome data enables comprehensive long-term follow-up.The observational design reflects real-world clinical practice across academic and non-academic centres.Owing to the rarity of SEIC, the anticipated sample size is limited, which may restrict statistical power for subgroup and multivariable analyses.Central pathology review is strongly recommended but not mandatory, and treatment allocation is not protocol-mandated, introducing potential diagnostic heterogeneity and confounding by indication.

## Introduction

 Serous endometrial intraepithelial carcinoma (SEIC) (Tumor characteristics were coded according to the International Classification of Diseases for Oncology (ICD-O) code 8441/2) is defined as a non-invasive lesion of the endometrial epithelium, replacing the native surface of the endometrium.^1
2^ A p53 mutation is often present, diagnosed through immunohistochemistry, which classifies SEIC in the p53 mutant endometrial tumours.^3
4^ Despite its non-invasive nature, SEIC exhibits malignant potential and poor prognosis, with documented cases of extrauterine dissemination even at presentation.^5–8^ Published case series and a recently published review have recommended performing surgical staging as primary treatment.^1
7
9–12^ In the Netherlands, clinical management varies from therapeutic hysteroscopy to surgical staging procedures.^13^ International guidelines lack specific recommendations for managing SEIC as a distinct entity. Although SEIC is currently defined as a non-invasive serous lesion, it is increasingly considered part of the serous, p53-mutated endometrial tumours rather than as a distinct entity.^12
14
15^ The collaborative guideline for managing patients with endometrial carcinoma by the European Society of Gynaecological Oncology, European Society for Radiotherapy and Oncology, and European Society of Pathology positions SEIC-equivalent FIGO IC (stage IC according to the International Federation of Gynecology and Obstetrics staging system) serous lesions in a grey zone of ‘uncertain risk’ due to insufficient outcome data, underscoring the lack of consensus and the evolving nature of its classification. This guideline has no explicit management recommendations for the uncertain risk category.^15^ The National Comprehensive Cancer Network guideline in the USA advises surgical staging and adjuvant therapy for all serous carcinoma FIGO 1A or higher, without a distinct section dedicated to SEIC management.^16
17^ Surgical staging, whether performed via laparotomy or minimally invasive techniques, entails a comprehensive procedure associated with recognised risks of complications.^18
19^ The impact of surgical staging on SEIC survival outcomes remains uncertain due to limited data. Lymph node sampling, especially lymph node dissection, lacks clear evidence, leaving ambiguity about SEIC metastasis to pelvic or para-aortic/paracaval nodes. Bilateral sentinel lymph node sampling has also been recommended, as sentinel lymph node procedures are increasingly performed for endometrial carcinomas.^12^ We propose that superficial intraepithelial carcinoma may disseminate via the fallopian tubes into the peritoneal cavity. Consequently, the necessity of lymph node sampling or dissection in SEIC treatment remains uncertain. In our recently published retrospective cohort study, 23 patients diagnosed with SEIC were evaluated, revealing no evidence of disease dissemination at the time of surgery. Over a follow-up period of nearly 3 years, no disease recurrences have been documented.^20^ Since complete staging did not detect any metastasis in this study it might be safe to omit standard staging procedure and to perform a simple hysterectomy with peritoneal washings and peritoneal biopsies (including biopsy of the infracolic omentum). Therefore, the primary objective of this study is to establish an international registry and longitudinally monitor patients diagnosed with SEIC, thereby contributing to the augmentation of knowledge and improvement of treatment strategies. This study establishes a registry for longitudinally monitoring of patients with non-invasive serous carcinomas/SEIC. By evaluating surgical and systemic treatments, we aim to enhance knowledge and refine treatment strategies, ultimately impacting patient survival outcomes and quality of life (QoL). Because the terminology may be further consolidated in the coming years, this study uses the combined term ‘non-invasive serous carcinoma’ including SEIC and FIGO IC serous carcinomas, and includes all lesions meeting the pathological criteria for SEIC, regardless of diagnostic nomenclature. This ensures compatibility with current and future classification systems. We hypothesise that patients with non-invasive serous carcinoma of the endometrium have a low risk of extrauterine disease and recurrence, and that less extensive surgical management may be associated with similar oncological outcomes while potentially reducing treatment-related morbidity and preserving QoL. This registry is designed to explore this hypothesis and generate evidence for future studies.

## Methods and analysis

### Study objectives

The aims of this registration study include: (1) To establish and maintain a prospective observational registry of patients diagnosed with SEIC and equivalent non-invasive serous tumours. (2) To systematically collect clinical, diagnostic, tumour, treatment and outcome data in patients with SEIC. (3) To evaluate the association between the extent of surgical treatment, the use of adjuvant therapy and progression-free survival (PFS).

### Study design

This is an observational cohort study conducted in the Netherlands, with the intention to expand into an international, multicentre registry. International centres with expertise in gynaecological oncology will be invited to participate using the same data collection framework. The estimated duration of the registration is 10 years: inclusion of participants during 5 years with a target follow-up duration of 5 years per participant. Regarding therapy of SEIC, all options are allowed (surgery, systemic therapy, radiotherapy). All interventions are part of regular medical treatment and are registered. This is an observational study; no interventions are performed.

### Study population

#### Inclusion criteria

Participants are eligible for inclusion if they meet all of the following criteria:

Histopathologically confirmed serous intraepithelial endometrial lesion, defined as:Serous morphology consistent with SEIC, including p53-abnormal immunophenotype and high-grade nuclear atypia.No evidence of stromal or myometrial invasion on histopathologic evaluation.Diagnosed using any of the following accepted diagnostic labels:SEIC.FIGO IC serous carcinoma.Serous carcinoma in situ.Minimal uterine serous carcinoma.≥18 years of age.Signed informed consent.

#### Exclusion criteria

Participants are not eligible for inclusion if they meet one of the following criteria:

Any diagnosis other than a non-invasive serous intraepithelial endometrial lesion, including:Endometrioid carcinoma.Clear-cell carcinoma.Serous carcinoma with invasion.Carcinosarcoma.Endometrial hyperplasia or endometrial intraepithelial neoplasia.Cases in which histopathology shows (also) myometrial or stromal invasion, even if previously labelled SEIC.

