### Outcomes

#### Primary and secondary outcome

The primary outcome is PFS, defined as the time from histopathological diagnosis of the lesion to the first occurrence of disease progression, recurrence or death from any cause, whichever occurs first. Disease progression or recurrence is defined as radiologically, histologically, or clinically documented local, regional or distant disease. Patients without an event will be censored at the date of last follow-up. Secondary outcomes include overall survival (OS), disease-related symptoms, health-related QoL, type and extent of surgical and adjuvant treatment, severe postoperative complications (Clavien-Dindo grade III–IV), and treatment-related adverse events associated with systemic therapy or radiotherapy classified according to the Common Terminology Criteria for Adverse Events (CTCAE) version 5.0.^22
23^ OS will be defined as the time from histopathological diagnosis to death from any cause. Study outcomes/endpoints include the baseline characteristics of patients, diagnostic measurements, treatment details and follow-up data.

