### Data collection and data management

#### Data collection

All eligible patients who provide informed consent will be included in a secure online database using Castor EDC. Clinical data will be collected through e-CRFs completed by the treating gynaecologist at the participating centre. The coordinating investigator will review all entered data to ensure completeness and consistency. Participants will complete validated online questionnaires via Castor EDC at baseline (prior to treatment, if applicable), and at 6 months, 2 years and 5 years after diagnosis.

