#### Collected variables

Baseline characteristics include age, body mass index, type of physical complaints, medical history, use of medication and Eastern Cooperative Oncology Group (ECOG) performance status (known as WHO performance score).^24^ Diagnostic measurements include imaging details (date of imaging, results of gynaecological examination and advanced imaging), biochemical laboratory results and histopathology results of endometrial biopsies and surgical specimens. Regarding the histopathological examination, the following data will be obtained: the histomorphological characteristics, immunohistochemistry staining on mismatch repair proteins (MMR) and p53 mutation and results of molecular diagnostics (MSI test, p53 mutation analysis, POLE mutation analysis). Treatment details include details on the surgical treatment (date, type of surgical procedure (hysteroscopy, hysterectomy with/without salpingo-oophorectomy, staging procedure, cytoreductive surgery), perioperative findings (dissemination of disease and FIGO stage of disease), and perioperative complications) and details on administered adjuvant therapy (date, duration and type/regimen of adjuvant therapy). Given anticipated changes in FIGO and WHO terminology, all cases will be stored with raw histopathology and molecular data, allowing for retrospective reclassification according to future systems. Follow-up data will be collected at 6 months, 2 years and 5 years after diagnosis and include clinical status, symptoms, QoL, evidence of disease recurrence and disease-related or unrelated death.

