#### Pathology data and biological material

In the Netherlands, pathology data are registered in the Dutch Nationwide Pathology Databank (PALGA). Pathology results from referring centres will be entered into the e-CRF. Access to PALGA’s internal database by members of the research team will only occur if participants have provided explicit consent and if necessary for completeness of data. For international participating centres, e-CRFs will be completed by the treating clinician or pseudonymised pathology reports will be securely transmitted to the coordinating investigator. Additional diagnostic analyses (eg, immunohistochemistry, mutation analysis, MSI testing) may be performed if not previously available. Results and images will then be stored in the secure internal pathology database of Erasmus MC. Pathology specimens are coded using original pathology (T-)codes and stored in accordance with routine clinical practice for a minimum of 10 years. Use of residual material for additional analysis will only occur if participants provide consent. Participating centres are strongly encouraged to involve pathologists with expertise in gynaecological pathology. Whenever feasible, cases will undergo review by a gynaecological pathologist with expertise in serous endometrial neoplasia. If this expertise is not available in the participating centre or within the regional gynaecological oncology network, central pathology review will be performed by the coordinating research team of the Erasmus Medical Center. Any diagnostic revisions following expert review will be documented in the registry. Furthermore, raw histopathological and molecular data will be collected to facilitate reassessment and future reclassification where necessary. The T-code is not directly linked to hospital patient identifiers and can only be linked to study IDs by authorised pathologists.

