### Statistical analysis

Baseline characteristics, treatment details and outcome measures will be analysed using descriptive statistics. Continuous variables will be summarised using means and SD or medians and IQRs, as appropriate. Categorical variables will be presented as frequencies and percentages. Longitudinal QoL scores will be summarised descriptively over time. Comparisons between groups, if applicable, will be performed using the χ² test or Fisher’s exact test for categorical variables and the unpaired T-test or Mann-Whitney U test for continuous variables, depending on data distribution. If subgroup analyses are feasible, patients will be stratified according to the extent of surgical treatment (eg, complete surgical staging vs hysterectomy with bilateral salpingo-oophorectomy only). PFS and OS will be estimated using the Kaplan-Meier method, and differences between groups will be assessed using the log-rank test. Survival analyses will use the date of histopathological diagnosis as the index date. Univariate Cox proportional hazard regression analyses will be performed to explore potential predictors of survival outcomes. Multivariable Cox regression analysis will be conducted only if the number of events allows reliable modelling. Results will be reported as HRs with 95% CIs. All statistical analyses will be performed using the SPSS, V.25.0. A two-sided p<0.05 will be considered statistically significant.

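### The no-invasion criteria do not say which specimen or time point decides; if later surgical specimens count, patients with occult invasion drop out only when the uterus is removed

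*Protocol article*

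**What the plan says.** Under Inclusion criteria the protocol article requires "No evidence of stromal or myometrial invasion on histopathologic evaluation". Under Exclusion criteria it lists invasive serous carcinoma and, as a further item, "Cases in which histopathology shows (also) myometrial or stromal invasion, even if previously labelled SEIC". Neither list names the deciding specimen or the time of judgement.

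Under Primary and secondary outcome, progression-free survival (PFS) is "defined as the time from histopathological diagnosis of the lesion to the first occurrence of disease progression, recurrence or death from any cause". Overall survival has the same start, and Statistical analysis repeats: "Survival analyses will use the date of histopathological diagnosis as the index date".

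That date can precede definitive surgery:
- Data collection places the questionnaires "at baseline (prior to treatment, if applicable), and at 6 months, 2 years and 5 years after diagnosis".
- Collected variables includes "histopathology results of endometrial biopsies and surgical specimens".
- Sample size calculation expects more diagnoses to come from polyp resection.

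The Introduction says that in the Netherlands "clinical management varies from therapeutic hysteroscopy to surgical staging procedures", and Collected variables records hysteroscopy as one of the surgical procedure types. The third aim under Study objectives is to relate extent of surgery and adjuvant therapy to PFS.

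On changed diagnoses, Pathology data and biological material says: "Any diagnostic revisions following expert review will be documented in the registry". No section says whether a patient upgraded at surgery stays in follow-up or in any analysis.

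**The concern.** The phrase about an earlier SEIC label lets the exclusion reach back over a diagnosis already made. Read that way, eligibility depends on a finding that arises after time zero and that is available only under some treatments. A patient whose hysterectomy specimen shows invasion leaves the cohort. A patient with the same biopsy and the same hidden lesion, treated by hysteroscopy alone, stays, because the rest of the uterus is never examined.

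Two results are at stake. The first is the absolute risk of extrauterine disease and recurrence. The Introduction hypothesises that this risk is low and suggests that less surgery may be safe. For anyone diagnosed before surgery, extent of surgery is chosen before final histology exists, so the risk relevant to that choice includes patients who later prove to have invasion. Removing them moves the estimate towards the study's own hypothesis. The second is the third aim: in any comparison that includes hysteroscopy-only patients, that group alone would keep its occult invasive cases.

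**Working it through.** The document states no figure for this mechanism and makes no power calculation, so there is nothing to reproduce. Its only size statement is about 100 eligible Dutch patients with about 75% consenting: 0.75 × 100 = 75.

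**Order of events in the text**
1. Time zero is the histopathological diagnosis (Primary and secondary outcome; Statistical analysis).
2. The diagnosis may rest on a biopsy or polyp (Collected variables; Sample size calculation), with baseline data taken before treatment (Data collection).
3. Surgery follows and ranges from hysteroscopy upwards (Introduction; Collected variables).
4. Histology showing invasion excludes the case despite the earlier label (Exclusion criteria). Only a removed uterus allows this check throughout.

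**Illustration of size (all inputs assumed; none is in the documents)**
- q = share of biopsy-diagnosed patients with occult invasion: 10%, 20%, 40%.
- r0 = 5-year PFS event risk without invasion: 5%.
- r1 = the same risk with invasion: 20% or 40%.
- h = share treated by hysteroscopy only: 20%.
- Surgery has no effect on the event risk, and occult invasion is unrelated to the choice of surgery.

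Formulas:
- Risk in all biopsy-diagnosed patients, and in the hysteroscopy-only group: R = (1 − q)·r0 + q·r1.
- Risk left in the hysterectomy groups after exclusion: r0.
- Apparent risk ratio, hysteroscopy-only versus hysterectomy: R / r0.
- Pooled risk after exclusion: [h·R + (1 − h)(1 − q)·r0] / [h + (1 − h)(1 − q)].

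Lowest case (q = 10%, r1 = 20%): R = 0.90 × 0.05 + 0.10 × 0.20 = 0.065. Ratio = 0.065 / 0.05 = 1.3. Pooled = (0.2 × 0.065 + 0.8 × 0.9 × 0.05) / (0.2 + 0.8 × 0.9) = 0.049 / 0.92 = 5.3%.

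Highest case (q = 40%, r1 = 40%): R = 0.60 × 0.05 + 0.40 × 0.40 = 0.19. Ratio = 0.19 / 0.05 = 3.8. Pooled = (0.2 × 0.19 + 0.8 × 0.6 × 0.05) / (0.2 + 0.8 × 0.6) = 0.062 / 0.68 = 9.1%.

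| q | r1 | All biopsy-diagnosed (R) | Hysterectomy groups after exclusion | Pooled after exclusion | Spurious ratio |
|---|---|---|---|---|---|
| 10% | 20% | 6.5% | 5.0% | 5.3% | 1.3 |
| 10% | 40% | 8.5% | 5.0% | 5.8% | 1.7 |
| 20% | 20% | 8.0% | 5.0% | 5.7% | 1.6 |
| 20% | 40% | 12.0% | 5.0% | 6.7% | 2.4 |
| 40% | 20% | 11.0% | 5.0% | 6.8% | 2.2 |
| 40% | 40% | 19.0% | 5.0% | 9.1% | 3.8 |

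As a check, r0 = r1 = 10% gives 10% in every column and a ratio of 1.0 for every q, so there is no bias when invasion carries no extra risk.

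If 75 patients were all biopsy-diagnosed and 80% had a hysterectomy, the rule would remove 75 × 0.80 × q, which is 6 patients at q = 10% and 24 at q = 40%. The documents do not give the biopsy-diagnosed share, so these are upper figures for each q.

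**The case against.** **The exclusion is worded as an entry criterion.** A reader might infer that the protocol removes enrolled patients once surgery shows invasion. No section says so. The clause about an earlier label could refer to histology already revised before consent, for instance after expert review. If eligibility is judged once, at consent, patients upgraded afterwards also stay in the operated groups. This stands, and it is why the point is conditional. It does not remove the problem: inclusion would then depend on whether consent came before or after surgery, which is also not fixed.

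**The target is non-invasive disease.** Excluding invasive carcinoma is the disease definition. A reader might infer that the registry understates the risk of confirmed non-invasive lesions. It does not; the understatement concerns patients whose diagnosis rests on a biopsy.

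**The one named contrast is safe.** Statistical analysis gives, as an example, full staging against hysterectomy with bilateral salpingo-oophorectomy. Both groups yield a uterine specimen, so this mechanism does not distort it. Hysteroscopy versus hysterectomy is never named. It could enter under the third aim, which sets no limit on extent, but the number of such patients is unknown.

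**Safeguards exist, and analysis sets may be defined elsewhere.** Raw histology is stored and revisions are documented, and the article acknowledges diagnostic heterogeneity and confounding by indication. These measures help with reclassification, and analysis sets are commonly left to an analysis plan. However, eligibility is stated here, and a later analysis cannot recover outcomes that were never collected on excluded patients.

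**Conclusion.** The concern holds in conditional form. The eligibility text leaves the deciding specimen and time point open. If later surgical specimens count, the registry selects on a post-diagnosis finding that only removal of the uterus fully provides. Risks for patients deciding on a biopsy diagnosis are then too low, and hysteroscopy-only patients look worse than they should in any comparison that includes them.

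Under the assumed inputs the spurious risk ratio is 1.3 to 3.8. The 5-year event risk of a biopsy-diagnosed cohort falls from 6.5-19.0% to 5.3-9.1% pooled. A reader might infer that the registry would report the pure non-invasive risk (5% here), but that would require every patient to have had a hysterectomy. The figures show what is possible, not what is expected, and the bias vanishes if invasion does not change the risk. Clarification is inexpensive and bears on the third aim and on the low-risk hypothesis.

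**What to change.** 1. State that the no-invasion requirement in the inclusion list, and both invasion items in the exclusion list (invasive serous carcinoma, and invasion despite an earlier SEIC label), are judged on the index diagnostic specimen.
2. Keep, flag and follow patients who qualify on that specimen and are upgraded at later surgery. Report the upgrade rate with an exact 95% confidence interval.
3. Report extrauterine disease and PFS in two sets: (1) all patients with a qualifying pre-operative specimen, from diagnosis; (2) patients confirmed non-invasive on a hysterectomy specimen, with follow-up starting at hysterectomy so that set membership is known at time zero.
4. Restrict extent-of-surgery comparisons to set 2.

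The cost is wording changes to several criteria, one flag in the electronic case report form, follow-up of some upgraded patients, and the loss of hysteroscopy-only patients from the comparisons. Study status gives recruitment as May 2026 to April 2031, so an early change limits the outcome data lost.
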